
**Fig 1 pone.0310795.g001:**
[figure not shown]
Participant journey: Navigating through the study.

### Interventions

The participants in the Gita group will be imparted the teachings of the second chapter of the Bhagavad Gita (all verses) for 1 week, for 60 minutes per day. The teachings of the Bhagavad Gita will be imparted by a trained teacher and the second chapter has been chosen as it is said to contain the essence of the entire Bhagavad Gita [16]. The participants in the Kuchipudi group will be taught the Kuchipudi dance choreography to a popular devotional song (“Sivashtakam”, choreographed by Padma Bhushan [name] [name], song duration is approximately 10 min) for 60 minutes per day by a trained teacher for 1 week. Every day for 1 week, the participants in the Both group will be taught the Kuchipudi dance choreography to a popular devotional song (“Vandanamu Raghunandana”, choreographed by Kala Tilakam [name], song duration is approximately 5 min), which is shorter in duration than the song used in the Kuchipudi group, for 30 minutes by a trained teacher, followed by imparting the teachings from selected verses of the second chapter of the Bhagavad Gita (Verse 40–72) for 30 minutes by a trained teacher. The participants in the control group will receive no intervention. The participants will be instructed to join their assigned groups at the scheduled meeting times using the meeting link in their sealed envelopes. Apart from the teaching sessions, meetings will also be scheduled one day before the start of the teaching sessions, one day after the end of the teaching sessions, 40 days after the end of the teaching sessions, and 1 year after the end of the teaching sessions for the purpose of recording the baseline, immediate post-intervention, delayed post-intervention, and long-term follow-up measurements, respectively. For participants in the control group, the meeting schedule will consist of only the four measurement sessions.

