### Primary analysis

GEE Framework: The primary outcome, psychological distress as measured by the K10 scale, will be analyzed using the GEE framework. Robust standard errors will be used to account for correlated data due to repeated measures. An exchangeable correlation structure will be assumed.Primary Comparisons: Comparisons will be made between each intervention group (Gita, Kuchipudi, and Both) and the control group. Within each intervention group, comparisons over time (pre-intervention, immediate post-intervention, 40 days post-intervention, and 1-year post-intervention) will be performed.Pairwise Post-Hoc Comparisons: Pairwise post-hoc comparisons will be conducted following significant GEE results to identify specific group differences. The Bonferroni correction will be applied to control for the risk of type I error in these multiple comparisons.

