### Timeline

Engagement with PEHs begins in Week 1, followed by a 4-week recruitment period. Baseline measurements will be conducted in Week 5, interventions in Weeks 6–7, and post-intervention assessments in Weeks 8, 12, and 56. Interim analysis shall be conducted in Weeks 13–19, and results will be published as the Stage II of this registered report. Final analysis will be conducted in Weeks 57–61, and results shall be published as a brief report. Conferences, meetings, workshops, and other community engagement events to disseminate the results of the study will be ongoing indefinitely, starting from the date of publication of the interim analysis as a registered report. The detailed timeline is shown in Fig 3.

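### The active arms are taught in live online groups, but the analysis and sample size allow only for correlation within a person, so any class or teacher effect makes standard errors too small.

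*Protocol article*

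**What the plan says.** **Delivery.** Allocation is individual, by sealed envelope with a Zoom link inside (Participants). Under Interventions, "The participants will be instructed to join their assigned groups at the scheduled meeting times using the meeting link in their sealed envelopes". Each taught component has its own mention of a teacher:

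- Gita arm: "The teachings of the Bhagavad Gita will be imparted by a trained teacher".
- Kuchipudi arm: "for 60 minutes per day by a trained teacher for 1 week".
- Gita half of the Both arm: "Verse 40–72) for 30 minutes by a trained teacher".
- Control arm: "For participants in the control group, the meeting schedule will consist of only the four measurement sessions".

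The article does not say how many classes or teachers each arm has, or whether the Both arm shares teachers with the single arms.

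**Analysis.** The article prints a statistical analysis plan. Under Primary analysis, "Robust standard errors will be used to account for correlated data due to repeated measures", and "An exchangeable correlation structure will be assumed". The formula under Sample size calculation likewise allows only for correlation between measurements on the same individual. Class and teacher appear in none of Data analysis, Primary analysis, Subgroup analyses, Sensitivity analyses, or Strengths and limitations. The contamination section concerns information passing between arms, which is a different matter.

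**The concern.** Randomisation makes participants independent at entry. It does not keep them independent once they have spent a week in the same live class. A good or poor teacher, a supportive or disruptive peer group, or a failed connection moves everyone in that class together. The variance of an arm mean then has a between-class part that does not shrink as more people join the same class. Robust standard errors clustered on the person do not capture it.

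Two things are at stake. The first is error control: p-values and confidence intervals for the taught arms would look more precise than they are. The second is attribution. Gita versus Kuchipudi is half of the central research question, and Table 1 also tests Both against each single arm. If few classes or teachers deliver each content, a difference between them can pass for a difference between contents.

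**Working it through.** **Inputs from the protocol article.** Two-sided 5% level; 54 per group required; 64 per group recruited with 16% dropout expected, so 64 × 0.84 = 53.8, or about 54 analysed.

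**Assumed inputs.** The article gives no ICC for class and no class size. I take an ICC of 0.01 to 0.10 and two layouts: one class of 54 per arm, and about five classes of 11 per arm.

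**The plan's own figure.** The printed formula does not give 54. V_eff = 55/2.5 = 22.0 (22.5 is printed), and 7.84 × 22.5/12.25 = 14.4 (53.3 is printed). That is a separate error. Here 54 serves only as the stated number to be analysed.

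**Formulas** (normal approximation, one comparison of two arm means, class ignored in the analysis):

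- Design effect in a taught arm: D = 1 + (m − 1) × ICC, with m the class size.
- True variance over assumed variance, taught arm versus control: R = (D + 1)/2, because controls have no class.
- The same ratio between two taught arms: R = D.
- True two-sided error of a nominal 5% test: 2 × [1 − Φ(1.96/√R)].

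Example, m = 54 and ICC 0.02: D = 1 + 53 × 0.02 = 2.06. Against control R = 1.53, 1.96/√1.53 = 1.58, error 11.3%. Between taught arms R = 2.06, 1.96/√2.06 = 1.37, error 17.2%.

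| Class size | ICC (assumed) | D | 54 per arm is worth (54/D) | Error, taught v control | Error, taught v taught |
|---|---|---|---|---|---|
| 54 | 0.01 | 1.53 | 35 | 8.1% | 11.3% |
| 54 | 0.02 | 2.06 | 26 | 11.3% | 17.2% |
| 54 | 0.05 | 3.65 | 15 | 19.9% | 30.5% |
| 11 | 0.01 | 1.10 | 49 | 5.6% | 6.2% |
| 11 | 0.02 | 1.20 | 45 | 6.2% | 7.4% |
| 11 | 0.05 | 1.50 | 36 | 8.0% | 11.0% |
| 11 | 0.10 | 2.00 | 27 | 11.0% | 16.6% |

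**What a model can repair.** With several classes per arm, between-class variance can be estimated and carried into the standard error. With one class per arm it cannot, because class and arm are the same variable, and neither a larger sample nor another model separates them.

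**Simplifications.** The calculation covers a single post-teaching comparison before any Bonferroni correction. It treats controls as independent, although their measurement sessions are also scheduled online meetings. It includes no extra correlation between classes that share a teacher.

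**The case against.** The strongest objection concerns how much the text supports. A reader might infer that each arm is a single class of 64 with its own teacher, so that teacher and class are fully confounded with intervention. The singular teacher and the meeting link in each envelope point that way, but the article never says so. Blinding and Risk mitigation strategy speak of teachers in the plural, there are two cities, and consent forms exist in five languages. Nothing says that teachers differ between arms. An article may also leave class counts and teacher rosters to a fuller protocol. This stands: full confounding can be stated only conditionally. A class of 64 also uses recruited rather than expected analysed numbers, so 54 is the fairer upper case.

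It is equally fair that no ICC is available and that with small classes and a low ICC the error is close to nominal (5.6%). This stands too.

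Two tempting remedies are weaker than they look. Sharing teachers between a single arm and the Both arm helps only the Both comparisons; the Gita and dance teachers stay separate in Gita versus Kuchipudi. Nor does "interventions in Weeks 6–7" simply leave room for two successive runs. Timeline puts baseline in Week 5 and the first post-test in Week 8, while Interventions wants them one day before and one day after teaching. A Week 6 run would miss the post-test timing and a Week 7 run the baseline timing, unless measurements are staggered as well.

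None of this answers the core point. Live group teaching is stated, and the printed analysis names within-person correlation as the only kind it handles.

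**Conclusion.** The point holds in conditional form. The analysis and sample size omit class-level correlation in the taught arms, so if any exists, standard errors are too small for each taught arm against control and for every comparison between taught arms.

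The size rests on assumed ICCs and class layouts. With one class of about 54 per arm and ICC 0.01 to 0.05, true error is about 8% to 20% against control and 11% to 30.5% between taught arms, and class and teacher cannot be separated from arm. With about five classes of 11 and ICC 0.01 to 0.10, it is about 5.6% to 11% against control. The documents do not show which layout applies, so they do not establish that arm and teacher are fully confounded. This is an inexpensive improvement to make before teaching starts, since class structure cannot be changed afterwards.

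**What to change.** 1. Run several classes per taught arm concurrently in the same teaching week. If runs must be successive, stagger baseline and post-test with each run so that the one-day timing holds.
2. Assign class at random through a class-specific link in the envelope. If classes are split by language or city, keep a separate envelope set for each, so that nobody draws a class in the wrong language.
3. Record class and teacher for every taught participant.
4. Analyse K10 with the mixed-effects model already named under Sensitivity analyses, adding a random effect for class in the taught arms only (a partially nested model), with small-sample degrees of freedom.
5. Where feasible, share teachers between each single arm and the Both arm, recognising that this helps only the Both comparisons. For Gita versus Kuchipudi, use more than one teacher per content.
6. If only one class or one teacher per content is used, state in the plan and the report that the result cannot be separated from that class or teacher.

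The cost is some added timetabling, two data fields, revised analysis wording and somewhat wider confidence intervals. Teaching content and session length do not change.

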### Outcomes and measures

The primary outcome is psychological distress measured by the Kessler scale of psychological distress (K10) in this study. The K10 is a 10-item questionnaire that measures psychological distress based on questions about anxiety and depressive symptoms. It has previously been used in research conducted with PEH [17, 18]. At the immediate post-intervention, delayed post-intervention, and long-term follow-up measurements, apart from the K10, the participants will be asked if they have continued practicing the techniques learned during the intervention (Kuchipudi group: continued practice of the choreography, Gita group: continued self-reflection on the teachings of the Bhagavad Gita, Both group: continued practice of the choreography and continued self-reflection on the teachings of the Bhagavad Gita, and control group: none). The study flowchart is presented in Fig 2.

**Fig 2 pone.0310795.g002:**
[figure not shown]
Study flowchart.

### Data collection and management procedures

During each scheduled measurement session, the participants will be asked to take the questionnaire they were provided with in the sealed envelopes given to them at the time of enrolment that is pre-filled with the date of the appropriate measurement session. They will then be asked to hold the questionnaire sheet with the date visible to the camera and trained research support staff will check that each participant is holding the correct questionnaire. They will then walk the participants through how to fill in the questionnaire. Once they confirm that the questionnaires have been filled, they will walk the participants through how to take a photograph of the sheet and send the photo to the staff member via WhatsApp. Once the staff member receives legible photographs of the filled questionnaires from all participants, the meetings will be ended. The project staff will then save the photographs into as portable document format files on a secure computer situated in the research office of our organization and print out the same for our records. Our organization’s policy is to store both soft and hard copies of all research material—the soft copies are stored for a period of 2 years and the hard copies are stored for a period of 10 years. The research team will have unrestricted access to the final dataset.

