### Participants

Persons meeting the criteria for the definition of a houseless person—someone who does not live in a building or "census houses," but rather in the open or seeks shelter in public places such as railway stations, under flyovers, places of worship, etc.—according to the 2011 Census of India, and residing in Chennai or Dhanbad, India during and after the Unlock 2.0 phase of the COVID-19 pandemic in India, aged >18 years will be recruited. Persons with a formal diagnosis of anxiety, depression, and any other mental illness will be excluded from the study and provided access to evidence-based treatments. All PEH availing the services of Samanjasa Foundation in Chennai and Dhanbad will be approached to participate in the study; the study information will be disseminated through the case workers. During earlier studies we found that this strategy ensures nearly 90% response rate; therefore, we are expecting a similar enrolment rate in this study as well. The participants will be divided into four groups—the Bhagavad Gita (Gita), Kuchipudi dance (Kuchipudi), both Bhagavad Gita and Kuchipudi dance (Both), and control groups—in a 1:1:1:1 ratio. The participant identification number, group assignment, four copies of a questionnaire with pre-filled participant ID and follow-up date, meeting schedule, and Zoom meeting link will be sealed in a small envelope and the envelopes will be placed in a fishbowl and shuffled. The participant ID will be generated in a random order by an independent statistician using a pseudo-random number generator script in Python 3.9.13. Group assignment will be generated in sequence by the independent statistician; the participant ID generated first will be associated with the Gita group, the second with the Kuchipudi group, the third with the Both group, the fourth with the Control group, the fifth with the Gita group, and so on. The project staff will fill and seal the envelopes with the respective contents. Once a participant provides written informed consent to participate in the study, they will be asked to pull an envelope from the fishbowl and not reveal its contents to the research team. They will also be instructed not to read the questionnaires until the sessions scheduled for the purpose of filling them out. To monitor and minimize the risk of contamination, especially given the potential for participants within the same community to communicate, the project staff will send weekly text messages to the participants regarding not sharing details about the intervention with anyone, including their family members. Additionally, the project staff will randomly contact three participants from each group via a phone call every two months and ask them if they had heard anything about the interventions in the other study groups. Furthermore, during community events and interactions, case workers will be asked to assess the level of knowledge regarding the intervention among the PEH. The participant journey is illustrated in Fig 1.

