## Blinding

The study will involve three separate teams—trained teachers, project staff, and the research team. Trained teachers will be responsible for administering the interventions; the teachers will be blinded to the K10 results. Project staff will be responsible for ensuring participant compliance, collecting the filled K10 questionnaires as photos via WhatsApp, and printing the photos and storing them until data analysis; project staff will be blinded to data analysis. The research team will be responsible for study design, participant recruitment, obtaining written informed consent, data analysis and reporting; the research team will be blinded to participant group allocation.

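### All four dated K10 sheets are handed out at enrolment and only photos are described as collected, so earlier answers may be at hand at follow-up and the 1-year form must be kept for about a year

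*Protocol article*

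**What the plan says.** Under Participants, the project staff fill each envelope with the group assignment and "four copies of a questionnaire with pre-filled participant ID and follow-up date", together with the meeting schedule and link. After consenting, participants draw an envelope: "they will be asked to pull an envelope from the fishbowl and not reveal its contents to the research team". The one handling rule given is that the questionnaires are not to be read before the session at which they are filled in.

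Under Data collection and management procedures, participants at each session "take the questionnaire they were provided with in the sealed envelopes given to them at the time of enrolment", choosing the one dated for that day. Staff check on camera that it is the right one and guide completion. They then help the participant to "take a photograph of the sheet and send the photo to the staff member via WhatsApp". The meeting closes once legible photos have arrived from everyone. The archive's hard copy is a printout of the photo.

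The Blinding section describes the staff's task in the same way: "collecting the filled K10 questionnaires as photos via WhatsApp, and printing the photos and storing them until data analysis".

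The Plan for handling missing data and protocol deviations covers written instructions, reminders, data recharges and technology failure. It does not mention a lost or spoiled sheet.

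**The concern.** Two things follow if the procedure is carried out as described.

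First, a participant who has kept the papers has one completed K10 within reach at the immediate post-intervention visit, two at 40 days and three at 1 year. The rule against reading ahead concerns sheets not yet due, and does nothing about sheets already filled in. K10 is the primary outcome and the only scale described under Outcomes and measures. It is self-reported, and participants know their group. Repeating earlier answers would pull change towards zero. Deliberately marking lower than last time in a taught group would exaggerate change. Either would also affect the within-person correlation, which the sample size section takes to be 0.5.

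Second, the 1-year measurement depends on a person living in the open or in public places producing one particular dated sheet about a year after receiving it. A participant who has lost it has no described way to complete the visit, so missing data could arise from logistics alone.

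**Working it through.** **Exposure to earlier answers.** The recruitment target is 256 participants, with four measurement sessions each (Sample size calculation; Interventions).
- Planned forms: 256 × 4 = 1,024.
- Follow-up forms: 256 × 3 = 768.

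The 768 is a ceiling. It assumes that everyone attends every visit and keeps every completed sheet.

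**How long the 1-year sheet must be kept: published calendar.** The Timeline gives a 4-week recruitment period before baseline in Week 5, and the last assessment in Week 56. I take enrolment as Weeks 1 to 4.
- Longest: 56 − 1 = 55 weeks. Shortest: 56 − 4 = 52 weeks.
- With the 4-week extension, enrolment can run over Weeks 1 to 8 and the last visit moves to Week 60. Longest: 60 − 1 = 59 weeks. Shortest: 60 − 8 = 52 weeks.

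**How long the 1-year sheet must be kept: definition of the visits.** Under Interventions, baseline is one day before teaching, teaching lasts one week, and the last visit is one year after teaching ends.
- Enrolled on the day of baseline: 7 days to the end of teaching + 365 = 372 days (53.1 weeks).
- Enrolled 28 days before baseline: 28 + 372 = 400 days (57.1 weeks).

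The two ranges differ because one year after teaching that ends in Week 7 falls at about Week 59, not Week 56. On either basis the sheet is kept for about a year.

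**Slack at 1 year.** The plan recruits 64 per group, expects 16% dropout, and states a need for 54. I take the 54 as stated and do not examine its derivation here.
- Expected to remain: 64 × 0.84 = 53.8 per group, already just under 54.

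The documents give no rate of sheet loss. The rates below are assumptions, taken as additional to the 16%.

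| Assumed loss among those retained | Completeness at 1 year | Per group |
|---|---|---|
| 5% | 0.84 × 0.95 = 79.8% | 53.8 × 0.95 ≈ 51 |
| 10% | 0.84 × 0.90 = 75.6% | 53.8 × 0.90 ≈ 48 |
| 20% | 0.84 × 0.80 = 67.2% | 53.8 × 0.80 ≈ 43 |

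**Is paper return described anywhere?** Data collection and management procedures has the photo sent, saved and printed. Blinding has the staff "printing the photos and storing them until data analysis". Neither section has the completed sheet coming back, and in both the stored hard copy is a print of the photo.

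**The case against.** The strongest objection is that retention of the paper is inferred from silence. This is a journal article, its participant-journey figure and flowchart are not shown, and return of used forms or a stock of spares could sit in an operations manual. That stands as a limit. A reader might infer that the plan says sheets are never collected, and it does not say so. The point survives because the article sets out the collection route step by step and describes it as photographic. Handing out all four sheets at enrolment, and requiring the matching one at each visit, is stated outright.

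A reader might also infer that the design inflates the effect of the taught groups. The documents do not support a direction: copying and deliberate lowering work against each other, and an unblinded participant can mark low without an old sheet. Completion is also supervised on camera.

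The two harms partly exclude each other, since someone who has lost the papers has no completed sheets to copy. The 768 forms and the loss rates should therefore not be added together as if both applied to everyone. What the 16% covers is not stated, and it might already include some lost sheets. The planned reminders, staff follow-up and data recharges should help attendance, but they do not replace a missing sheet.

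**Conclusion.** The concern holds as a weakness in the measurement procedure that should be corrected. It does not show that the results will be biased or that the trial will be underpowered. As described, earlier answers can be at hand at up to three of four visits, with an effect on change in K10 of unknown direction and size. The 1-year sheet must survive about a year: 52 to 55 weeks on the calendar, up to 59 with the extension, at least 372 days by the visit definition. Any loss beyond the planned 16% takes the 1-year groups further below the stated 54.

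This rests on two assumptions: that the described photo-only collection is the whole procedure, and that sheet loss is not already counted in the dropout allowance. It is worth acting on before enrolment because answers influenced by an earlier sheet cannot be corrected in the analysis.

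**What to change.** Amend Participants and Data collection and management procedures as follows.

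- Take the follow-up questionnaires out of the enrolment envelope. Issue a blank K10 for each session just before it, by default as a form or image over the WhatsApp channel already in use.
- Have project staff hold spare paper blanks, so that a lost sheet does not mean a missed visit.
- Once staff have confirmed a legible photo and saved it, ask the participant to delete the sent image from the phone. Retrieving paper alone would leave the answers in the message thread.
- Ask for the completed sheet back at the next routine case-worker contact where feasible. Do not have it destroyed: Data cleaning resolves discrepancies against the original data source. Do not make hand-over compulsory either, given the logistical difficulties with face-to-face sessions described in the Introduction.
- Extend the existing instruction so that participants are told not to consult earlier answers.

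The cost is a change of wording and modest extra staff handling before each session, with no added participants, visits or analyses. Earlier answers become less available but cannot be ruled out entirely.
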